## Abstract

**Background:**

Existing therapeutic interventions to treat diabetes are well known, yet the majority of people with diabetes do not consistently achieve blood glucose targets (even individual therapy targets) for optimal health, despite the large range of treatment options available. Such outcomes have remained stubbornly poor for decades with <25% adults with diabetes achieving glycaemic targets. Patient behaviour, individually supported in routine clinical care, is an important missing component to improved outcomes, in a medical healthcare model not ideally suited to supporting successful diabetes management.

**Methods:**

A multi-centre, parallel group, individually randomised trial comparing consultation duration in adults with type 1, type 2 or pre-diabetes using the Spotlight Consultations pre-clinic assessment compared to usual care in the Spotlight-AQ study. Two hundred adults with type 1, type 2 or pre-diabetes attending routine care outpatient appointments across up to ten participating sites will be invited to participate.

**Intervention:**

An outpatient pre-clinic intervention delivered within 1 week prior to scheduled routine outpatient appointment.

**Primary outcome measure:**

Duration of routine outpatient consultation.

**Secondary outcome measures:**

Functional health statusDiabetes distressDepressionTreatment satisfactionImpact on self-care behavioursHCP burnoutHCP treatment satisfaction and burdenHypoglycaemia (time less than 70mg/dL)Hyperglycaemia (time above 180 mg/dL)Change in weightChange in HbA_1c_Cost effectiveness of intervention

**Discussion:**

Results from the study will provide valuable insights into patient-professional communication practices within routine care and recommendations will be made, as necessary, for improvements to that. If the intervention is shown to be clinically and cost-effective, the feedback from participants and healthcare professionals will be used to make any improvements prior to its deployment to support improved communication and associated health outcomes.

**Ethics and dissemination:**

The trial was approved by the Wales REC7 Research Ethics Committee (21/WA/0020). Results will be disseminated through national and international conferences, scientific journals, newsletters, magazines and social media. Target audiences include consultants and other clinicians in diabetes, and medical professionals or scientists overall.

**Trial registration:**

ISRCTN15511689. Registered on 10 November 2021

## Introduction

### Background and rationale

There is an urgent need to develop interventions that lead to sustained improvements in glycaemic and quality of life outcomes for people with diabetes and that support diabetes prevention. Therapeutic interventions to treat diabetes have been shown to be effective in clinical trials, yet >75% of people with diabetes consistently do not achieve blood glucose targets (even individual therapy targets) for optimal health, despite the large variety of drugs, including insulin, and medical devices available, e.g. insulin pumps [1]. Such glycaemic outcomes have remained stubbornly poor for decades and are a significant risk factor for microvascular and macrovascular outcomes. Patient behaviour, individually supported in routine clinical care, is an important missing component to improved outcomes, in a medical healthcare model poorly suited to supporting successful diabetes management.

As such, it is important to recognise the different needs of each individual and support skills development so that individuals are empowered to undertake effective disease self-management. Data from the International Diabetes Federation (IDF) shows that 10% of global health expenditure is spent on diabetes (US $760 billion), predicted to rise to $825bn by 2030 [2]. Indirect costs from premature death, disability and other health complications due to diabetes are estimated to add an additional 35% to the annual global health expenditure associated with the condition [2]. The intangible costs, however, are less visible but include worry, anxiety, discomfort, pain, loss of independence, concerns about managing the condition, fears for future complications and their potential impact on quality of life. These are also significant contributors to the cost of diabetes.

Depression is commonly reported to be 2–3 times more prevalent in people with diabetes than the general population [3]. This figure perhaps overshadows the significant number of individuals who do not report symptoms of depression, but experience diabetes distress. These emotions can be described as feeling overwhelmed and defeated by diabetes; feeling angry about diabetes, frustrated by the self-care regimen and/or having strong negative feelings about diabetes; feeling that diabetes is controlling their life; worrying about not taking care of diabetes well enough, yet unable, unmotivated or unwilling to change; avoiding diabetes-related tasks that give feedback about consequences of poor control; and/or feeling alone/isolated with diabetes. In type 2 diabetes (T2D), distress (but not depression) was related with poor glycaemic control and change in distress (but not change in depressive symptoms) was associated with both short- and long-term changes in glycaemic control [4]. Similar relationships were found in type 1 diabetes (T1D): diabetes-specific emotional distress (measured by the Diabetes Distress Scale) was related to glycaemic control in a Norwegian study and was also linked to worsening diabetes management over time in adults with T1D [5]. There are no existing standardised or validated strategies used in routine care to minimise the impacts of diabetes distress [6].

Routine patient care visits currently leave both patients and healthcare professionals feeling frustrated both in primary and specialist care settings. The lack of understanding of the psychosocial burden of diabetes and the evolving consequences results in a negative impact on clinical practice with consequential negative outcomes for patients and increasing frustration for healthcare professionals. Complex and detailed algorithms are supplied by various guidelines for the management of blood glucose, lipids, blood pressure and long-term complications, but these relate only to medical management. Even goals which have been mutually agreed upon are often not followed up, leaving patients frustrated and healthcare professionals struggling to provide tailored support. Typically, physicians interrupt their patients 11 s after they start describing their problems; approximately half of patients’ concerns are not discussed; and in half of health care visits, patients and physicians disagree on the central problem presented [7]. Disagreement about treatment goals, inconsistency amongst healthcare teams and confusion about treatment priorities are associated with poorer outcomes [6].

Burnout amongst healthcare professionals is a key challenge affecting healthcare practice, safety and quality of care. It is estimated that more than half of US physicians experience substantial symptoms of burnout, with burnout almost twice as prevalent amongst physicians as US workers in other fields [8]. Nurses experience a similarly high prevalence of burnout and depression, with 43% reporting high degrees of emotional exhaustion. COVID has exacerbated this problem. Furthermore, there are significant correlations between a physician’s sense of depersonalisation and patient satisfaction with their hospital care, and between a physician’s job satisfaction and patient satisfaction with their healthcare and patient-reported adherence to medical advice [8].

### Objective

The aim of the current study is to evaluate the clinical and cost-effectiveness of validated patient report outcome (PROs) pre-clinic assessment measures to identify patient priority concerns and mapped to evidence-based, theory-driven and resources to address those concerns. This addresses an urgent unmet need in routine care to improve communication and understanding for both people with diabetes and healthcare professionals.

## Trial design

Spotlight is an exploratory multicentre, parallel group, individually randomised RCT. Sites are primary and secondary care NHS centres located in Southampton, Wessex, Portsmouth, Bradford, Blackburn and South-West London. It will compare consultation length, biomedical and psychosocial outcomes in adults with type 1, type 2 or pre-diabetes attending routine outpatient appointments for their diabetes care. The number needed for a two-sample *t* test with standardised effect size of 0.50 at alpha=0.05, 90% power is 86 per group [9]. Thus, we will recruit a minimum of 100 participants for the control group and 100 participants for the intervention groups to allow for potential dropout. Previous feasibility data from real-world evidence collection has demonstrated feasibility, acceptability and improved consultations across three centres in the UK and USA [10].

## Study setting

The study will be conducted in primary and secondary care settings within England. A list of study sites can be found in the supplementary material.

## Eligibility criteria

### Inclusion criteria

≥18 years. There is no upper age limit.Diagnosed with T1D or at risk of or diagnosed with T2D (including pre-diabetes) for at least 6 months.Currently receiving any diabetes treatment.Willing/able to use Spotlight Consultations tool.Ability to give informed consent.Ability to speak and read English fluently.

### Exclusion criteria

<18 yearsLack of capacity

## Recruitment

### Screening and consent

Outpatient diabetes surgery appointment clinic lists will be scrutinised ahead of appointments and for people who appear eligible. An information sheet explaining the trial will be sent by post or email as appropriate (including contact details to opt out if the person does not want to be contacted about the trial). Potential participants who are approached have all consented to be contacted to discuss the study further. Before the outpatient appointment, a member of the research team will contact the prospective participant to discuss the study at least 24 h before the outpatient appointment allowing sufficient time for reflection and discussion. This will allow those who are eligible for the study to be randomised immediately after the outpatient appointment. If the participant wishes to take part, they will have the opportunity to discuss the study face-to-face with a research nurse before they give written consent. Final eligibility criteria will be checked before the participant is recruited. Patients whose medical records cannot be accessed prior to the appointment to determine eligibility (e.g. patients from another hospital) will be given information about the study on the day of their outpatient appointment and will be offered the opportunity to come on another day to discuss their participation in the trial. Research nurses at each participating centre will obtain informed consent from trial participants.

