### Randomisation

Once the consent process has been completed, study participants will be randomised into either the intervention group or control group for 12 months. We will randomise on a 1:1 basis using computerised randomisation software. Sealed envelope online software randomisation will be used. Randomisation is blocked and stratified by centre (using random permuted blocks) to ensure groups are balanced.

Those randomised to the intervention group will be asked to complete study questionnaires every three months and the Spotlight Consultation pre-clinic assessment at baseline and follow-up scheduled routine outpatient appointments (Table 1). The results of the Spotlight Consultation digital health assessment will be discussed between the participant and healthcare professional during the outpatient visit along with identified matched care pathways and agreement made on best-fit action plan.

**Table 1 Tab1:** Psychosocial questionnaires

Construct	Measure	Relibaility
Diabetes Distress	DDS [11]	*α*’s=.94
Depression	PHQ-2 [12]	*α*’s=.86
Anxiety	GAD-7 [13]	*r* = 0.782
Engagement	Self-Care Inventory (SCI) [14]	*R*=0.89
Treatment Satisfaction/Utility	Diabetes Treatment Satisfaction Questionnaire [15]	*a* = 0.92
Health Resource Utility	EQ5D [16]	*α*’s=.89
Well-being	WHO-5 [17]	*α*’s=.90
HCP Burnout	Maslach Burnout Inventory [18]	*α*’s=.90

All measures will be administered at baseline, 3, 6, 9 and 12 months

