## The spotlight consultations intervention

### Intervention arm

Participants who are randomised to receive the Spotlight Consultations intervention will be sent a unique secure link to the Spotlight-AQ platform. The platform is commercially available and owned by [name]. The intervention consists of a validated pre-clinic questionnaire that provides insights into individual patient priority concerns across core domains of diabetes management. These priority concerns are presented graphically and form the basis of the discussion within the routine outpatient consultation. Mapped evidence-based resources are available to the HCP to share with their patient based on agreed goals set.

Telemedicine or in clinic visits: Participants will have a telemedicine or in-person clinic visit as per their usual routine care during the trial. Study participants will complete a personal assessment on study tablet devices if face-to-face visit. The support of a research assistant will be available if required. HCPs will also access the results and care pathway options, via their own secure portal logins. HCPs and participants will discuss the priorities and possible options collaboratively in a co-decision making, person-centred approach. Participants will be invited for repeat assessment as per routine care.

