### Control arm

Participants in the control group will continue to receive usual care. Control group participants will be offered access to the Spotlight platform and pre-clinic assessment at the end of the RCT, for use in their next schedule routine outpatient appointment.

Implementing usual care appointments or the outpatient pre-clinic intervention (delivered within one week prior to scheduled routine outpatient appointment) will not change actual treatment for diabetic patients and these will continue for both trial arms.

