### Follow-up

After the participants are randomised to either the intervention or control arm, data will be collected from them at the following timepoints:Pre scheduled routine outpatient appointment (baseline)Three, 6, 9 and 12 months post-randomisation

Participants will be sent reminders to complete follow-up questionnaires a week after they are due, as necessary.

There will be no special criteria for discontinuing or modifying allocated interventions.

Types of data that will be collected from medical records and questionnaire data, in addition to the baseline questionnaires that will be repeated, will be:MortalityAdverse eventsHealth economic questions (adapted CSRI (client survey receipt inventory) questionnaire)

Healthcare professional questionnaire data (Maslach burnout inventory) will be collected at baseline, 6 and 12 months. A sub-group of six k healthcare professionals involved in the delivery of the intervention will be interviewed once around 12 months after the start of the trial in their centre.

The primary outcome data, i.e. length of each consultation, is collected using a stopwatch by participating healthcare professionals and recorded in the study records by the clinical trials team. All other outcome data is electronic and data analysts are not blinded; thus, unblinding will not occur.

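### Randomisation is placed after the outpatient appointment in one section and must precede it in others, so a pre-allocation consultation could be counted in the primary outcome

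*Protocol article*

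**What the plan says.** All references are to the protocol article.

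- **Screening and consent** describes a contact at least 24 h before the outpatient appointment and gives its purpose: "This will allow those who are eligible for the study to be randomised immediately after the outpatient appointment".
- **Randomisation** ties allocation to consent only: "Once the consent process has been completed, study participants will be randomised into either the intervention group or control group for 12 months". It then has the intervention arm complete "the Spotlight Consultation pre-clinic assessment at baseline and follow-up scheduled routine outpatient appointments", with the results discussed during the visit.
- **Abstract, Intervention**: "An outpatient pre-clinic intervention delivered within 1 week prior to scheduled routine outpatient appointment". **Control arm** repeats this timing: "delivered within one week prior to scheduled routine outpatient appointment".
- **Intervention arm**: "Participants who are randomised to receive the Spotlight Consultations intervention will be sent a unique secure link to the Spotlight-AQ platform". Participants seen face to face complete the assessment on a study tablet.
- **Follow-up**: "After the participants are randomised to either the intervention or control arm, data will be collected from them at the following timepoints". The first timepoint on that list is the baseline, set before the scheduled appointment; the others are 3, 6, 9 and 12 months after randomisation. The same section says that the length of each consultation is timed by stopwatch as the primary outcome data.
- **Outcome measures** names the primary outcome as the duration of the routine outpatient consultation, without saying which one.

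**The concern.** The tool depends on allocation: only those randomised to it receive the link. Someone randomised after an appointment cannot have used it beforehand, and the duration of that consultation is a pre-randomisation value in both arms. If it enters the primary analysis, the expected difference between arms for it is zero, and the estimated effect is pulled towards no difference.

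Sites could also read the text differently. Some might allocate before the visit and others after it, so that the timed consultation would mean different things at different centres.

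A lesser matter is that the Follow-up section, read literally, collects baseline questionnaires after allocation. The allocation is open and the scales are self-reported, so knowing the arm could shift the baseline scores.

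**Working it through.** **1. Order of events, section by section**

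| Section | What it fixes | Allocation relative to the appointment |
|---|---|---|
| Screening and consent | Randomised straight after the appointment | After |
| Abstract (Intervention); Control arm | Tool delivered within one week before the appointment | Before |
| Intervention arm | Link sent only to those already randomised to it | Before |
| Randomisation (second paragraph) | Tool used at the baseline appointment and discussed there | Before |
| Follow-up | Pre-appointment baseline listed among data collected after randomisation | Before |
| Randomisation (first sentence) | Randomised once consent is complete | Either |

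If all sections refer to the same appointment, the first row conflicts with the next four, and the last row does not settle it. The first row also covers patients who are informed only on the day and invited back to discuss the trial. For them, that day's appointment necessarily precedes consent and allocation.

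**2. The plan's own sample size**

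Inputs from Trial design: standardised effect d = 0.50, alpha = 0.05, power 90%. Statistics gives a two-sided test; Randomisation gives 1:1 allocation.

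- Normal approximation: n = 2(1.960 + 1.282)² / 0.50² ≈ 84.1, rounded up to 85 per group.
- Exact t test: 85.03, rounded up to 86 per group.

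The stated 86 is reproduced. Exact power is 90.3% with 86 per group and 94.0% with 100 per group. The point below does not depend on any error in the sample size.

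**3. Illustration of dilution**

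Assumption: a share f of the timed intervention-arm consultations precedes allocation and carries no effect, and the SD is unchanged. The document gives no value for f. The effective standardised difference is d(f) = 0.50 × (1 − f). By the normal approximation, power ≈ Φ(d(f) × √(86/2) − 1.960), with √43 = 6.557.

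| f | d(f) | d(f) × 6.557 | Power, normal | Power, exact t |
|---|---|---|---|---|
| 0% | 0.500 | 3.279 | 91% | 90% |
| 10% | 0.450 | 2.951 | 84% | 84% |
| 25% | 0.375 | 2.459 | 69% | 69% |
| 50% | 0.250 | 1.639 | 37% | 37% |

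**The case against.** **The sections might be compatible.** A reader might infer that the stated orders are flatly impossible together. The document does not support that, because it never says that the appointment in Screening and consent is the timed one. It could be a recruitment visit: the person is randomised after it, sent the link, and uses the tool in the week before the next scheduled appointment, which is then called baseline. This reading is possible but nowhere stated. It also fits awkwardly with follow-up counted from randomisation, because the visit called baseline would come one appointment interval after randomisation. What stands is that the sequence is contradictory on its plain reading and the index visit is not identified.

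**It may be a slip in one sentence.** Most of the text points to allocation before the consultation. The article also has surgical wording (surgical complications in the Health economic analysis, pre-operative control in Statistics), which makes carry-over plausible. That origin is only an inference, but it favours an inconsistency in wording over a deliberate design. A site would still act on the sentence as written.

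**The loss of power might be overstated.** A reader might infer that power falls to the 5% type I error rate. That needs every analysed consultation to precede allocation, which the intervention description contradicts. Nor does the document say that consultations before and after allocation are averaged. Timing each consultation describes data capture, and the analysis plan, not shown here, may name the one to be analysed. A pre-allocation duration used as a covariate would do no harm and could add precision.

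**Post-allocation baseline scores do not bias the primary result.** A reader might infer that they do. The stated primary analysis adjusts for the stratification factors, meaning centre, and consultation duration is not self-reported. The matter is limited to self-reported secondary outcomes and the baseline covariates of the economic regression.

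**Conclusion.** The point holds as an internal inconsistency that reaches the primary outcome. Screening and consent puts allocation after the appointment, while the intervention as described needs it before, and no section says which timed consultation is the outcome. Followed literally, the Screening and consent text lets a consultation that could not carry an intervention effect into the primary comparison, biasing the result towards no difference.

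The size cannot be fixed from the document. The fall in power to about 69% or 37% rests on assumed shares of 25% or 50% and an unchanged SD, and shows only that a modest share would matter. The contradiction itself needs no assumption beyond reading the appointment as the same visit throughout. The baseline questionnaire issue is secondary.

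**What to change.** - Reconcile Screening and consent, Randomisation, Control arm and Follow-up to one order: consent, baseline questionnaires, randomisation, Spotlight assessment (intervention arm only), timed consultation.
- In Screening and consent, replace the clause on randomising after the appointment. Place randomisation after consent and baseline questionnaires and before the timed consultation, either ahead of the visit or on the same day. Allocation need not happen at the earlier contact, since face-to-face participants can complete the assessment on a tablet at the visit.
- Define the primary outcome as the duration of the first routine consultation after randomisation.
- For anyone already randomised after an appointment, exclude that consultation from the outcome and use the next one. Any duration recorded at the excluded visit may serve as a baseline covariate.
- Completing the baseline questionnaires before allocation also prevents knowledge of the arm from affecting the baseline scores of the self-reported secondary outcomes.

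**Cost.** For new participants, this takes a change of wording and a site instruction, using the existing online randomisation system, with no extra participants. Trial status gives recruitment from 18 October 2021 to 31 March 2022, so for people already enrolled the randomisation time must be checked against each timed consultation. Where the next consultation was not timed, the outcome would be missing.

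### Screening and consent places randomisation after the outpatient appointment, while the rest of the protocol needs allocation before it; the order must be reconciled and the primary outcome limited to post-randomisation consultations

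*Protocol article*

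**What the plan says.** All places are in the protocol article.

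- **Screening and consent:** people are identified from clinic lists and contacted at least 24 h before the appointment. The section then says: "This will allow those who are eligible for the study to be randomised immediately after the outpatient appointment". This is the only sentence that explicitly places the act of randomising relative to the appointment.
- **Randomisation:** "Once the consent process has been completed, study participants will be randomised into either the intervention group or control group for 12 months". Nothing here ties this to the appointment. The intervention arm then completes "the Spotlight Consultation pre-clinic assessment at baseline and follow-up scheduled routine outpatient appointments", and the results are discussed during the visit.
- **Abstract (Intervention) and Control arm:** the intervention is "delivered within 1 week prior to scheduled routine outpatient appointment", and the main text repeats this ("delivered within one week prior to scheduled routine outpatient appointment").
- **Intervention arm:** "Participants who are randomised to receive the Spotlight Consultations intervention will be sent a unique secure link to the Spotlight-AQ platform".
- **Follow-up:** data collection is described as following randomisation. The baseline time point is before the scheduled appointment, and the 3, 6, 9 and 12 month points are counted from randomisation. On the primary outcome: "The primary outcome data, i.e. length of each consultation, is collected using a stopwatch".

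**The concern.** Spotlight reaches a participant only after allocation and is meant to shape the consultation that follows within a week. A consultation that ended before allocation cannot have been shaped by it. If sites follow the Screening and consent sentence, the consultation for which a person was screened is unexposed in both arms, and its stopwatch time is a baseline measurement.

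Two things are at stake. First, the primary outcome is consultation duration, and the Follow-up section treats the length of each consultation as primary data without excluding one held before randomisation. Including such a visit adds a comparison whose expected difference is zero and pulls the estimate towards no effect. Second, first use of Spotlight would wait for the next routine visit while the follow-up clock already runs from randomisation, so early secondary outcomes could be measured before any exposure.

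**Working it through.** **1. Order of events, side by side**

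| Section | Order stated or implied |
|---|---|
| Screening and consent | appointment → randomisation |
| Randomisation | consent → randomisation → Spotlight at the baseline appointment |
| Intervention arm | randomisation → link sent |
| Abstract (Intervention); Control arm | Spotlight → appointment, within one week |
| Follow-up | randomisation → baseline data → scheduled appointment |

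Read together, the last four rows give consent → randomisation → link and assessment → appointment. The first row does not fit that sequence if the appointment is the same one.

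**2. The plan's own sample size**

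Inputs from Trial design: standardised effect 0.50, alpha 0.05, power 90%. The Statistics section makes the test two-sided, and Randomisation gives 1:1 allocation. The exact two-sample t test solution is 85.03 per group, rounded up to 86, with power 90.3% at 86. The stated figure reproduces.

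**3. If the recruitment visit alone were analysed under the Screening order**

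The expected difference is 0, so the chance of a significant result is alpha, 5%, against the planned 90%.

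**4. If it were averaged with one later visit (illustration)**

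Assumptions, none of which is in the document: two consultations per person, equal weights, equal SD at each visit, and a true effect of 0.50 SD at the later visit only.

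- Mean effect: (0 + 0.50)/2 = 0.25 SD.
- SD of the mean of two visits with within-person correlation r: √((1 + r)/2).
- Standardised effect: 0.25/√((1 + r)/2).

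| r | Standardised effect | Power, 86 per group | Power, 100 per group |
|---|---|---|---|
| 0.3 | 0.310 | 52% | 59% |
| 0.5 | 0.289 | 47% | 53% |
| 0.8 | 0.264 | 40% | 46% |
| 1 (SD unchanged, extreme bound) | 0.250 | 37% | 42% |

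**5. The loss shrinks with more later visits**

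Take one index and two later visits at r = 0.5. The mean effect is (0 + 0.50 + 0.50)/3 = 0.333, the SD is √((1 + 2 × 0.5)/3) = 0.816, and the standardised effect is 0.408. Power at 86 per group is 76%. With the index visit left out, it is 0.50/√0.75 = 0.577 and 96%.

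**6. Exposure**

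The visit interval is not stated. Under the Screening order, if the next routine visit came 6 months after randomisation, the 3-month questionnaires would precede any Spotlight use. If it came at 12 months, the 3, 6 and 9 month questionnaires would.

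**The case against.** The strongest reply is that one sentence is out of step and the rest of the article shows the intended order. Follow-up puts it most directly: randomise, collect baseline, then the appointment. The article also carries text that does not fit this trial, such as surgical complications in the health economic section and pre-operative glycaemic control in the Statistics section, so the sentence may be a leftover. This largely stands. A reader might infer that the trial was run with consultations timed before allocation, or that the primary comparison is not randomised. The documents support neither: they show a contradiction, and consultations after randomisation give a valid comparison under either order.

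A second reply is that the sections describing delivery speak of a scheduled routine appointment without identifying it as the recruitment visit. A person could be randomised after one visit and use Spotlight before the next, which would then be the baseline visit. The text does not exclude this, so it is too strong to say that the two statements can never both be met. But the article does not say this either, and under that reading the follow-up clock would start before the first Spotlight consultation.

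A third reply is that which consultations enter the model belongs in the analysis plan, which is not shown. In general that is fair. Here, however, the protocol itself describes the primary data as the length of each consultation and elsewhere places randomisation after an appointment. The combination is wrong as written, whatever further detail is left to the analysis plan.

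The power figures are fairly called illustrative. The 37% figure in particular needs a within-person correlation of 1.

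**Conclusion.** The contradiction is real and touches the primary outcome. It is a conflict to reconcile; it does not show that the trial is biased. If the Screening and consent sentence governed and the recruitment consultation were counted, the primary estimate would be diluted. In the two-visit, equal-weight case the 0.50 SD effect is halved, and power at 86 per group falls from 90% to about 47% at r = 0.5, with 37% as the extreme bound. With more later visits the loss is smaller. These sizes rest on the assumed number of visits, weighting and correlation, and on the index visit being analysed as an outcome, none of which the protocol states. If allocation in fact preceded every timed consultation, nothing is lost and only the wording needs correction.

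**What to change.** 1. Replace the Screening and consent sentence so that the article gives one order throughout: consent, randomisation, pre-clinic assessment within the preceding week, timed consultation.
2. State in Follow-up that only consultations held after randomisation count towards the primary outcome.
3. Compare each participant's randomisation date with the consultation dates. Where a timed consultation came before randomisation, use it only as a baseline value, as a covariate in the planned ANCOVA, and never as an outcome.

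**Cost.** No extra participants. For some people, contact and consent must come earlier than the present 24 h minimum, so that the assessment can be sent and completed before the visit. This changes the recruitment workflow as well as the text. People who are first told of the study on the day of their appointment would have their first trial consultation at a later visit. The Trial status section gives recruitment completion as 31 March 2022. If recruitment has closed, the change of workflow no longer applies, and only the date check and the analysis rule remain to be done, ideally before the primary outcome is analysed.
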